## Abstract

**Background:**

There has been little development of the general practice consultation over the years, and many aspects of the present consultation do not serve communities with multiple health and social problems well. Many of the problems presenting to general practitioners in socio-economically disadvantaged areas are not amenable to a purely medical solution, and would particularly benefit from a multidisciplinary approach. Socio-economic deprivation is also associated with those very factors (more psychosocial problems, greater need for health promotion, more chronic diseases, more need for patient enablement) that longer consultations have been shown to address. This paper describes our study protocol, which aims to evaluate whether a lengthened multidisciplinary primary care team consultation with families in a socially deprived area can improve the psychological health of mothers in the families.

**Methods/Design:**

In a randomised controlled trial, families with a history of social problems, substance misuse or depression are randomly allocated to an intervention or control group. The study is based in three general practices in a highly deprived area of North Dublin. Primary health care teams will be trained in conducting a multidisciplinary lengthened consultation. Families in the intervention group will participate in the new style multidisciplinary consultation. Outcomes of families receiving the intervention will be compared to the control group who will receive only usual general practitioner care. The primary outcome is the psychological health of mothers of the families and secondary outcomes include general health status, quality of life measures and health service usage.

**Discussion:**

The main aim of this study is to evaluate the effectiveness of a lengthened multidisciplinary team consultation in primary care. The embedded nature of this study in general practices in a highly deprived area ensures generalisability to other deprived communities, but more particularly it promises relevance to primary care.

**Trial registration:**

Current Controlled Trials ISRCTN70578736

## Background

### The impact of socio-economic deprivation

There is little doubt that individuals living in areas of socio-economic deprivation suffer poorer health. [1] In 1980 the Research Working Group chaired by Sir Douglas Black produced an authoritative report documenting inequalities in health in Britain. [2] This stimulated a widespread response and since then much more evidence has accumulated about health inequalities in many different countries, [1] including Ireland. [3] In particular, both standardised mortality rates [4] and infant mortality rates [5] are correlated with socio-economic deprivation in Ireland. The all-cause mortality rate on the island of Ireland in the lowest occupational class is 100–200% higher than in the highest occupational group. [6] There is also evidence that morbidity is highest in general practices serving socio-economically deprived areas. This includes psychiatric morbidity, [7] cardiovascular disease,[8] diabetes, [9] cerebrovascular disease, [10] and psychological distress. [11] Inequalities in health are often compounded by inequalities in access to health care. In Dublin, for example, there is evidence that general practices are heavily concentrated in more wealthy areas. [12] Patients from deprived areas are also more likely to have higher consultation rates [13,14] and prescribing costs. [15] Individuals living in these areas have a higher need and use of social services. [16]

The National Health Strategy in Ireland *'Quality and Fairness' *has equity as one of its fundamental principles:

"Equity will be central to developing policies (i) to reduce the difference in health status currently running across the social spectrum in Ireland; and (ii) to ensure equitable access to services based on need". [17]

However, little of a concrete nature has been put in place to address this imbalance between health inequalities and access to health services. Primary and secondary care services are configured to give advantage to those with the least health need. There is little evidence from the literature in Ireland or the UK of attempts to reconfigure primary care in socio-economically deprived areas in order to address health inequalities.

### Consultation length

There have been several review articles of the impact of longer consultation length. [18-20] These conclude that longer consultation length includes more key elements of the consultation, particularly health promotion, health education, preventive measures, improved recognition and handling of psychosocial problems, fewer prescriptions, improved chronic disease management, and better patient enablement. Longer consultations are also associated with greater patient satisfaction and reduced doctor stress. Socio-economic deprivation is associated with those very factors (more psychosocial problems, greater need for health promotion, more chronic diseases, more need for patient enablement) that longer consultations have been shown to address. However, one study concluded that 'increasing socioeconomic deprivation was associated with higher prevalence of psychological distress and shorter consultations. This provides further evidence to support Tudor Hart's 'inverse care law' and has implications for the resourcing of primary care in deprived areas.' [21]

### Multidisciplinary working

Many of the problems presenting to general practitioners (GPs) in socio-economically disadvantaged areas are not amenable to a purely medical solution, and would particularly benefit from a multidisciplinary approach. There are few examples of adopting a multidisciplinary consultation in primary care. One study of a multidisciplinary consultation in Israel reported creating a multidisciplinary clinic in the community for frequent attenders. The intervention consisted of a comprehensive bio-psychosocial consultation where life history and medical symptoms were woven together into a new narrative. The intervention also included pharmacological treatment and short-term psychological interventions. Consultations and treatment costs fell by two thirds after one year. They concluded that the integrated approach of the clinic satisfied at least three needs: of the patient, of the referring physician and of the health maintenance organization. [22]

### Hypothesis

This study sets out to evaluate an alternative way of delivering primary care in a socio-economically disadvantaged community. The intervention incorporates both a multidisciplinary team approach to the consultation and a lengthened consultation time.

The null hypothesis is that implementation of a lengthened and multidisciplinary primary care consultation will have no impact upon the psychological health of mothers in terms of anxiety and depression as measured by the Hospital Anxiety and Depression Scale (HADS).

### Objectives

Our primary objective is to evaluate the effectiveness of a lengthened multi-disciplinary consultation in primary care with socially deprived families on the psychological health of the mothers in the family as compared with normal care. Our secondary objective is to assess the impact of the intervention on health status and quality of life; on health service use; and on health promotion outcomes including smoking, alcohol and substance use.

## Methods/Design

The study is a randomised, controlled, intervention trial where families (with at least one child under the age of 16 years) with a history of social problems, substance misuse or depression are allocated to one of two groups:

• Intervention group where families will receive a lengthened multidisciplinary consultation in primary care.

• Control group where families will receive usual GP care only.

### Ballymun Primary Care Implementation Project

Ballymun is a suburb of North Dublin, Ireland covering an area ofapproximately two square miles. It had a population of 16,568 at the 1996 census, with an atypical age profile. Thereis a disproportionately high proportion of females aged 20 to 49 and low proportion of over 65 year olds (3.1% compared to 11.4% in the State). There was a rise in lone parent families from 28% in 1991 to 37% in 1996. Almost half of all children in Ballymun are reared in lone parent families. Ballymun is an area of extreme deprivation with a HASSE deprivation index of 10 (equivalent to the highest deprivation ranking). This index measures educational attainment, housing and employment status. [23] The area is characterised by educational and economic disadvantage highlighted by the following points:

• High levels of early school leaving.

• Widespread and persisting school truanting.

• Poor levels of educational attainment.

• Low levels of transfer to third level education.

• Social welfare is the sole income of 71% of the population in Council accommodation.

• Very high unemployment rates.

As a consequence there are great health and social needs in the community. Health and social services are delivered from the local health centre and from a variety of other facilities in the town centre. Three general practices operate from the health centre and have a sole commitment to Ballymun. These are soon to be relocated into a purpose built Health Care Unit.

The three general practices were successful in becoming one of ten Primary Care Implementation Project under government policy in Ireland. [24] The project proposal incorporated the new Health Care Unit with capacity for the full range of primary care services, an integrated multidisciplinary team approach to primary care, and the development of disease prevention, rehabilitation and social services to complement the existing diagnosis and treatment focus. The multidisciplinary team will include GPs, practice nurses, public health nurses, physiotherapist, occupational therapist, social worker, community psychiatric nurses and dietician.

Ballymun is an ideal place to carry out this trial in view of its status as a Primary Care Implementation Project and its high level of socio-economic deprivation.

### Identification and recruitment of patients

Figure 1 shows the recruitment process of patients into the study.

**Figure 1 F1:**
[figure not shown]
Flowchart of study recruitment process.

The four participating GPs and the participating primary care team members in the three practices will identify eligible families and make an informal approach to ascertain interest in participation. They will provide lists of eligible families with a history of social problems, substance misuse or depression. Once a list of eligible families has been identified, mothers of the families will be invited to participate in the research by letter and subsequent telephone follow up. A description of the project will be provided with the letter. The letters will be on practice letterhead and signed by the GP. Patients respond by returning the expression of interest form to the research team. A researcher contacts all mothers who express interest in order to arrange an initial face-to-face interview. At this interview the study is fully explained, consent is obtained and baseline data is collected.

### Inclusion and exclusion criteria

All families attending the three general practices in Ballymun are eligible to participate. Families must include a mother and have at least one child under the age of 16 years. The families must also have social and/or mental health and/or alcohol and/or drug problems. Families are excluded if the mother of the family is under 18 years of age; where English is not the first language; where mothers have a learning disability or dementia; or where the family has a high financial income (defined as not being eligible for a GMS card – a means tested access to free medical care in Ireland – €266.50 per week threshold in 2006 for a single parent with dependent children).

### Primary outcome

The primary outcome of this study is the psychological health of mothers in terms of anxiety and depression as measured by the Hospital Anxiety and Depression Scale (HADS). [25] Mothers have been chosen for several reasons. Measuring the health of a 'family' is difficult so it was decided to look for a target member of the family. Mothers are a key axis to the health and health care of families. There is evidence that mothers in deprived settings have poor mental health, and it is suggested that improved well-being of mothers is seen as a key target for improved family health and lifestyle. [26] In addition, 50% of families in the Ballymun area are single parent families and it is likely that the majority of the single parents are mothers. The HADS was also chosen for several reasons. High levels of anxiety and depression are expected in mothers in this area. HADS has been widely used and validated in primary care settings and norms for communities are available. It was therefore decided that it would perform well as a measure in this study.

### Baseline assessment

Baseline data are collected from all study participants using questionnaires, GP computer records, and from the records of multidisciplinary team clinical meetings. Baseline assessment is conducted by a researcher and takes approximately one hour to complete.

Patient written consent is obtained prior to undertaking baseline assessment. Patients' baseline demographic details were taken upon recruitment: Age, marital status, employment status, number of children, and details of living accommodation, smoking status, and alcohol and drug history are noted. Health service use was also assessed by measuring the frequency of participants' GP and practice nurse visits. All patients' consultations with their GPs and practice nurses are held in the practice computer records. This allows the researcher to search for the number of GP and practice nurse attendances in the period 12 months prior to recruitment, and 12 months after. Three questionnaires were administered: Hospital Anxiety and Depression Scale [25] (HADS- a measure of anxiety and depression); SF36v2 [27] (a measure of general health status); and SEIQoL-DW [28] (a measure of quality of life).

### Outcome assessment

Data collected at baseline, including primary and secondary outcome measures, will be collected again at 6 and 12 months post-intervention for both the intervention and control groups. A researcher will collect 6 month and 12 month follow up data by face-to-face interview with the patient. We will also access administrative data sets in relation to health service use.

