### Randomisation

Families are randomised to either the intervention or control group after all baseline assessments are completed (figure 2). Following randomisation, families are informed by a letter from the principal investigator of whether their family will be in the intervention or control group.

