### The intervention

Families in the intervention group will be offered a multidisciplinary consultation with the Primary Health Care Team (PHCT) to assess their health and social needs. The multidisciplinary appointments with intervention patients will be in a phased manner to protect against major service disruption. The four GPs in the study will set aside one three hour session per fortnight each for the study. Intervention families will be presented and discussed openly at the regular Primary Health Care Team meetings in order to gain maximal input and advice. The PHCT will also decide during this meeting who will attend the consultation and arrange a time and date for it. The GP will inform the family, and confirm the time and date for the consultation with the family.

The PHCT members attending the consultation will meet 10 minutes prior to the consultation to discuss the family and appoint one member of the team to lead the consultation process. This member will make introductions, explain the process to the family and open the consultation. The consultation will follow the family's agenda. All areas of health and social functioning will be explored. An appropriate management plan will be made during the consultation and agreed with the family. This will also establish the need for further lengthened consultations with members of the primary care team. A written summary of the consultation should be made for research follow up purposes. Minimum detail should include date and duration of the consultation, team members present in the consultation, and the management plan or follow up agreed from the consultation.

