### Data collection, monitoring and analysis

Descriptive statistics will be used to summarise patient factors for the two study groups and to compare baseline variables between control and intervention group. Outcomes between study groups will be compared to assess the effect of the intervention. Primary and secondary outcome measures at 6 months and 12 months time frames will be compared between intervention and control groups adjusting for baseline values using an ordinal logistic regression model.

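### Follow-up is timed from the intervention in both arms, which leaves controls and families who never attend a consultation without a defined start date

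*Protocol article*

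**What the plan says.** Under Outcome assessment, the Protocol article says that the baseline data, including primary and secondary outcome measures, "will be collected again at 6 and 12 months post-intervention for both the intervention and control groups". The control condition, under Methods/Design, is: "Control group where families will receive usual GP care only".

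On sequence, the Randomisation section says: "Families are randomised to either the intervention or control group after all baseline assessments are completed". The consultation in the intervention arm comes after that. The section headed The intervention says that families are offered it, that "The multidisciplinary appointments with intervention patients will be in a phased manner to protect against major service disruption", and that "The four GPs in the study will set aside one three hour session per fortnight each for the study". It also says of the agreed management plan: "This will also establish the need for further lengthened consultations with members of the primary care team".

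Health service use has a different anchor. Under Baseline assessment, GP and practice nurse attendances are searched "in the period 12 months prior to recruitment, and 12 months after".

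The analysis section says: "Primary and secondary outcome measures at 6 months and 12 months time frames will be compared between intervention and control groups adjusting for baseline values". It does not say from which date the 6 and 12 months run.

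**The concern.** The rule for timing the primary outcome depends on an event that only one arm has. A control family has no consultation, so there is no date from which to count. A family randomised to the intervention that declines or never attends has no date either, although it belongs in the randomised comparison. Where the consultation does happen, more than one date could serve, because further lengthened consultations are foreseen.

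What is at stake is comparability of the arms in time since baseline. Families enter because they have social, mental health, alcohol or drug problems, and the practices are due to move to a new building, so HADS could change over time for reasons unrelated to the intervention. If one arm is measured systematically later, any such change is mixed with the treatment effect. Adjusting for the baseline HADS value does not adjust for elapsed time. HADS and service use would also describe different periods for the same family.

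**Working it through.** The article gives no figure for the lag, so there is none to reproduce. The check has two parts.

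**1. Can the stated rule be applied?**

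- Control family: no intervention takes place and no index date is assigned. The rule gives no visit date.
- Intervention family, one consultation: the date is the consultation date, at a variable interval after baseline and randomisation.
- Intervention family, several consultations: the date could be that of the first or the last.
- Intervention family, never attends: the rule gives no visit date.
- GP and nurse attendances, both arms: counted from recruitment. This can be applied to everyone, but it is not the HADS clock.

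**2. How long could the lag be?**

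Inputs from the article: 4 GPs, one three-hour session each per fortnight (The intervention); 46 families per arm (Sample size calculations). Assumptions: *k* families per session, with *k* = 1, 2 or 3; all 46 families ready at the same time; every session used.

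Time to clear the arm, in weeks = 2 × (46 / (4*k*), rounded up to whole fortnights). The mean wait is about half of that. Months are weeks / 4.345.

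- *k* = 1: 46/4 = 11.5, so 12 fortnights = 24 weeks (5.5 months); mean 12 weeks (2.8 months).
- *k* = 2: 46/8 = 5.75, so 6 fortnights = 12 weeks (2.8 months); mean 6 weeks (1.4 months).
- *k* = 3: 46/12 = 3.83, so 4 fortnights = 8 weeks (1.8 months); mean 4 weeks (0.9 months).

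What this means for the difference between arms depends on how controls are dated:

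- Controls dated from randomisation, intervention families from the consultation: the 6-month visit falls on average about 1 to 3 months later since baseline in the intervention arm, and up to about 5.5 months later for the last family in the slowest case.
- Control dates matched to those of intervention families, or a common calendar date for all: the mean difference is about zero.

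For the last family, and ignoring any gap between recruitment and randomisation, the part of the 12-month service-use window that precedes the consultation is 24/52 = 46% at *k* = 1, 12/52 = 23% at *k* = 2, and 8/52 = 15% at *k* = 3.

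**The case against.** A reader might infer that the arms are in fact measured at different times since baseline, with the intervention arm later and flattered by it. The article does not support that. It names the same two time points for both groups and leaves the control clock open. Matching controls to intervention families, or using a common calendar date, is compatible with the wording. The flowchart of the intervention process (Figure 2) is not shown and may indicate when controls are seen, and a full protocol may carry the scheduling rule.

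The lag figures are also fragile. Families per session is not given. The randomisation sentence can be read per family or for the whole cohort, and mothers are contacted individually as they express interest. If families are randomised as they enrol, the queue and the lag shrink. No rate of HADS change over time is stated, regression to the mean operates in both arms, and the move to the new building affects both. Nothing in the article says that non-attenders are excluded.

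A recruitment-based window for practice records is not an error in itself, since it applies equally to both arms. Finally, anchoring at randomisation has its own price: in the slowest case it shortens the time between consultation and 6-month visit considerably.

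All of this limits the claim about size and direction. It does not rescue the timing rule. The article does more than omit a detail: it states an origin that cannot be applied to controls or non-attenders. Nor does matching solve the problem for non-attenders, who have no consultation date to be matched to.

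**Conclusion.** The point holds as a fault in the stated time origin. For controls and for families who never attend, 6 and 12 months post-intervention is undefined; for families with several consultations it is ambiguous; and it differs from the recruitment origin used for service use. Unequal time since baseline is a risk, not an established fact: it follows if controls are timed from baseline or randomisation, and not if their dates are matched or set by calendar. The article describes neither approach.

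The mean lag of about 1 to 3 months, with 8 to 24 weeks to clear the arm, rests on the assumed 1 to 3 families per session and on all 46 families being ready together. The size and direction of any effect on HADS cannot be derived from the article. The sample size is not affected. The correction is still warranted before follow-up begins, because the rule governs the primary outcome, ties it to a post-randomisation event in one arm only, and cannot be fully repaired in the analysis once visits have been made on different clocks.

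**What to change.** Replace the timing sentence under Outcome assessment with a rule of this kind: outcomes are collected 6 and 12 months after randomisation in both arms, whether or not the consultation took place. Use randomisation as the origin for the service-use windows too (12 months before and 12 months after), and name it in the analysis section. Record the date of the first consultation for every intervention family, so that the lag can be reported.

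The cost is a change of wording and of the visit schedule. The downside is that late-phased families have less time after the consultation. In the slowest case above, the last family would reach its 6-month visit about 26 − 24 = 2 weeks after the consultation, and its 12-month visit about 52 − 24 = 28 weeks after it. For such families the 12-month visit is the more informative one. Randomising in batches as consultation slots open would shorten the lag, but it is optional and the fix does not depend on it.

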### Trial organization and management

The study has received ethics approval from the Research Ethics Committee of the Royal College of Surgeons in Ireland (Ref REC2004/115). No significant risks to participants are anticipated. As the study is unblinded and low risk a data monitoring committee is unnecessary.

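### Follow-up HADS is collected face to face in an unblinded trial, with no masking of the interviewer stated and no rule that allocation-revealing records are read only after the interview

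*Protocol article*

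**What the plan says.** All references are to the protocol article.

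- **Primary outcome:** the mother's anxiety and depression, measured by HADS, a subjective scale.
- **Outcome assessment:** "A researcher will collect 6 month and 12 month follow up data by face-to-face interview with the patient". The same section says "Data collected at baseline, including primary and secondary outcome measures, will be collected again at 6 and 12 months post-intervention".
- **Baseline assessment:** the data are gathered "using questionnaires, GP computer records, and from the records of multidisciplinary team clinical meetings", and "Baseline assessment is conducted by a researcher and takes approximately one hour to complete". HADS, SF36v2 and SEIQoL-DW are described as administered; who marks the answers is not said.
- **Randomisation:** this follows completion of baseline, and "families are informed by a letter from the principal investigator of whether their family will be in the intervention or control group".
- **The intervention:** families in the intervention arm are discussed at the primary care team's regular meetings. A summary of each multidisciplinary consultation, giving at least its date, its length, who attended and the agreed plan, is to be written for later research use.
- **Trial organization and management:** "As the study is unblinded and low risk a data monitoring committee is unnecessary". No exception is made for the person who collects outcomes.

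**The concern.** Mothers and clinicians in this trial cannot be blinded. The person who collects the primary outcome might be, and the article does not say that this is attempted. An interviewer who knows the arm can affect a mood questionnaire through prompting, explanation or tone, or simply through what the mother thinks the interviewer hopes to hear. If this differs between arms, it adds to or subtracts from the treatment difference, and the two cannot be separated afterwards.

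The route to unmasking is concrete. Team-meeting records are a named data source, and consultation summaries exist only for intervention families. Anyone who reads either before a follow-up interview may learn the arm.

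**Working it through.** The plan gives no figure on this point, so there is none to reproduce. The check is mainly a reading of the sections together.

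**1. Is an interviewer present when the primary outcome is taken?** Yes. Outcome assessment specifies a face-to-face interview at 6 and 12 months, and the baseline measures, HADS included, are repeated then.

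**2. Is that interviewer masked?** No masking is stated, and Trial organization and management calls the study unblinded without qualification.

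**3. Can records used in the study reveal the arm?**
- Baseline records cannot, because randomisation comes later.
- Team-meeting records made after randomisation can, because intervention families are discussed at those meetings.
- Consultation summaries can, because only intervention families are offered the consultation.

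**4. Are those records kept until after the interview?** No section sets an order.

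**5. Can the analysis repair it?** No. Data collection, monitoring and analysis plans an ordinal logistic regression adjusted for baseline values. Baseline HADS is measured before allocation, so it carries no information about a distortion that arises at follow-up and differs by arm.

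**6. What would a given bias do?** This is illustration only, since the article gives no size for the bias.
- Input from Sample size calculations: 46 per group, taken as stated. Whether 46 follows from the stated target is a separate question, and nothing here depends on it.
- Assumptions: no true effect, complete follow-up, a normal approximation, a two-sided 5% test (the article does not state sidedness), and a spurious shift of δ standard deviations.
- Standard error of the difference, in SD units: √(2/46) = 0.2085.
- λ = δ / 0.2085.
- False-positive rate = 1 − Φ(1.96 − λ) + Φ(−1.96 − λ).

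| Assumed δ | λ | False-positive rate |
|---|---|---|
| 0 | 0 | 5% |
| 0.1 | 0.480 | 0.0694 + 0.0073 = 7.7% |
| 0.2 | 0.959 | 0.1585 + 0.0018 = 16.0% |
| 0.3 | 1.439 | 0.3011 + 0.0003 = 30.1% |
| 0.5 | 2.398 | 66.9% |

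The article says that HADS is not normally distributed and plans an ordinal model, so the table shows order of magnitude only. It applies to a shift in either direction.

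**The case against.** **The word unblinded may mean less than it seems.** It appears in a sentence about the monitoring committee, and the unavoidable knowledge of families and GPs is enough to explain it. The article is condensed, and interview procedures may be set out in a fuller document. This stands in part: the article does not prove that the interviewer knows the arm. But it describes the whole study as unblinded and describes the mode of follow-up, and neither statement provides for masking.

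**A reader might infer that the interviewer reads the team-meeting records and so learns the arm before taking HADS.** The article does not say so. It lists "from the records of multidisciplinary team clinical meetings" as a baseline source in a passive sentence. The only record search it assigns to the researcher is of GP and practice nurse attendances. The repetition at 6 and 12 months could mean the same items and not the same sources. What stands is that the records can reveal allocation and that no order is set.

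**HADS may already be filled in by the mother.** Nothing says that items are read aloud, so part of the remedy may already be practice. If so, writing it down costs nothing.

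**A reader might infer that masking needs no extra staff, because the allocation letter comes from the principal investigator.** That is a judgement. Quality assurance speaks of one researcher. If that person also handles consultation summaries, or carries out the closing qualitative interviews with families and team members, keeping them masked could need a second worker.

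**Masking the interviewer leaves the respondent unmasked.** This stands in full. Mothers know their arm and rate themselves.

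**A reader might assume that the bias favours the new consultation, or express it as a share of the effect the trial is sized for.** Favouring the intervention is plausible, but the article does not establish it. It gives neither a HADS standard deviation nor a bias size, so any such share would rest on invented figures.

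**Conclusion.** The point holds in limited form. A subjective primary outcome is collected in person in a study described as unblinded. No masking of the interviewer is stated, and nothing keeps allocation-revealing records until after the interview. Interviewer bias can therefore enter follow-up HADS, and baseline adjustment cannot take it out.

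Its size and direction cannot be estimated from the article. The false-positive rates of about 8% to 67% for assumed shifts of 0.1 to 0.5 SD show only that even a modest bias would matter with 46 per group. They do not show that a bias of that size is present.

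It is not established that the interviewer knows the arm, that the interviewer reads the meeting records, or that masking is free of staffing cost. The change is worth making because it is specific and cheap; the gap does not invalidate the design.

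**What to change.** Amend Outcome assessment along these lines:

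> At the start of each 6- and 12-month visit the mother completes HADS herself, on paper, and seals it. If she needs help, items are read verbatim. Where feasible the interviewer is not told the family's allocation and asks the mother not to disclose it. GP, team-meeting and consultation records are extracted only after both the 6- and 12-month questionnaires are complete. Any unmasking is recorded, with its timing.

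The trial report should then give the proportion of interviews at which the interviewer was unmasked, by arm.

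**Cost.** This is mainly a change in mode and task order. Some mothers will need items read to them, and some will reveal their arm. Record extraction is delayed, but attendances are held in practice computer records and can be counted retrospectively. That existing staff can do all of this is an assumption. If one researcher must handle the records during follow-up, sealed self-completion at the start of the visit is still possible and limits that person's influence on HADS.

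**What it does not do.** It does not remove respondent bias. The report should state that limitation whatever is decided about masking.
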